Data collection will start in January 2022 and will finish in December 2022. Data will be collected at baseline, after 6 weeks of the intervention (Post-intervention I) and 24 weeks later (Post-intervention II; Figure 1). Data from participants will be obtained through self-reported questionnaires provided by researchers. Teachers at schools will assure the full completion of the questionnaires at the desired times (T1-T3). Data will be stored on a secure server during the study, following the Spanish regulations. Recruitment of participants will be reported according to CONSORT guidelines for clustered randomized trials (Ivers et al., 2011; Figure 2).

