#### Primary outcomes

3.5.1.

The level of resilience is the primary outcome, assessed using principally the Child youth resilience measure-32 (CYRM-32; Llistosella et al., 2019). Additionally, the Brief resilience scale (BRCS; Limonero et al., 2014) will be used.

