##### Child youth resilience measure-32

3.5.1.1.

The CYRM-32 is a 5-point Likert scale, optimized to assess resilience in children and young adults (aged 12–23). It has been previously shown that Cronbach’s *α* for the scale was 0.88, Confirmatory factor analysis supported a three-factor solution: family interaction (0.79 Cronbach’s *α*), interaction with others (0.72 Cronbach’s *α*) and individual skills (0.78 Cronbach’s *α*). Pearson correlation to assess temporal stability over 2 months was 0.695 (Llistosella et al., 2019).

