### Sample size calculation

3.6.

Standard deviation (SD) of the primary outcome CYRM-32 scale was used to estimate the minimum sample required to detect a 10-point difference in the scale between the intervention and control groups.

Taking into account an SD of 20 of the CYRM-32 scale, accepting an alpha risk of 5%, power of 80% and a follow-up loss rate of 10%, it would be necessary a minimum of 70 students/group. GRANMO tool (Antaviana, 2011) was used to calculate the sample size.

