### Data analysis

3.9.

An intention-to-treat analysis will be performed. A descriptive analysis of the variables will be carried out, with frequency and percentage for the qualitative variables; mean and standard deviation for the quantitative normal distributed variables and median and quartiles for the quantitative not-normal distributed variables. The values from the scores for the intervention and the control group will be compared with the *t*-student test if the score is normally distributed, with the Mann–Whitney test if the score is not-normally distributed and if the score has a cut-off, it will be compared with chi-square test. The effect size will be calculated as the difference of means and with ratio of proportions (with its corresponding confidence intervals).

A linear regression and a logistic regression will be considered including other variables that can affect the response. Also, we will stratify the results for other factors like gender, age and others than will be considered. To check normality, the Kolmogorov–Smirnov test and the Shapiro–Wilk test will be used. All the confidence intervals will be performed with a 95% confidence level. All the analysis will be performed with the software R version 4.2.2.

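### Section 3.9 commits only to an unadjusted two-group test and a raw mean difference, and does not fix the collected baseline CYRM-32 score as a covariate

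*Protocol article*

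**What the plan says.** - **Outcome and timing.** Section 3.5.1: "The level of resilience is the primary outcome, assessed using principally the Child youth resilience measure-32". Section 3.3: "Data will be collected at baseline, after 6 weeks of the intervention (Post-intervention I) and 24 weeks later". A baseline value of the primary scale is therefore part of the design.
- **Comparison.** Section 3.9 opens its rule with "The values from the scores for the intervention and the control group will be compared with the" and names the t-test for normally distributed scores and the Mann-Whitney test otherwise, with chi-square for scores that have a cut-off. On the estimate it says: "The effect size will be calculated as the difference of means and with ratio of proportions". None of these uses a covariate.
- **Adjustment.** The one sentence on models in section 3.9 is "A linear regression and a logistic regression will be considered including other variables that can affect the response". The variables are not named. No change score, analysis of covariance or baseline covariate appears anywhere in the article.
- **Stability of the scale.** Section 3.5.1.1: "Pearson correlation to assess temporal stability over 2 months was 0.695".
- **Allocation.** Section 3.7 allocates whole schools by computer-generated random numbers and describes no stratification or matching. Section 4 reports 674 participants in eight randomised schools, with the intervention delivered in four, which leaves four controls.

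**The concern.** A baseline measurement of the same scale is usually the best single predictor of the follow-up score, and this trial already collects it. A two-sample test of scores with a raw mean difference makes no use of it. Two things follow. First, outcome variance that baseline could explain stays in the error term. Second, with only four schools per arm, the arms can differ in baseline resilience by chance, and an unadjusted comparison of later scores carries the persistent part of that difference into the estimate.

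There is also a pre-specification issue. Section 3.8 says the research team is not blinded, and section 4 says baseline and first follow-up data are already being analysed. A regression that is only to be considered, with open covariates, can be chosen or dropped once the results are visible.

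**Working it through.** **Inputs from the article.** Section 3.6: difference 10, SD 20, alpha 5%, power 80%, loss 10%. Section 3.5.1.1: r = 0.695. Section 4: 674 pupils in 8 schools, so 674/8 = 84.25 per school and 337 per arm if the arms are equal (assumed).

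**Assumed, because the article gives none.** The ICC, and the school-level correlation between baseline and follow-up.

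**1. The plan's own sample size.** The aim was "to estimate the minimum sample required to detect a 10-point difference in the scale between the intervention and control groups".
- n per group = 2 × (1.960 + 0.842)² × 20² / 10² = 62.8, rounded up to 63.
- With 10% loss: 63 / 0.9 = 70, as stated. A two-sided alpha is needed; one-sided gives 50, then 56.
- The sample size therefore rests on the same unadjusted two-sample comparison.

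**2. What baseline explains at pupil level.** Residual variance fraction = 1 − r².
- r = 0.695: 1 − 0.483 = 0.517. The square root is 0.719, so the SE falls by about 28% and the residual SD goes from 20 to 14.4.
- r = 0.5 (assumed, to allow for decay by the later follow-up): 0.75. The square root is 0.866, so the SE falls by about 13%.

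**3. Chance baseline difference between arms.** SE = 20 × √[(2/337) × (1 + 83.25 × ICC)].

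| Assumed ICC | Design effect | SE (points) | 95% range | Chance of a gap of 5 or more |
|---|---|---|---|---|
| 0 | 1.00 | 1.5 | ±3.0 | 0.1% |
| 0.01 | 1.83 | 2.1 | ±4.1 | 2% |
| 0.02 | 2.67 | 2.5 | ±4.9 | 5% |
| 0.05 | 5.16 | 3.5 | ±6.9 | 15% |
| 0.10 | 9.33 | 4.7 | ±9.2 | 29% |

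**4. Gain from adjustment in the cluster design.** Take ICC 0.05 and 84.25 × 0.9 = 75.8 pupils per school at follow-up. In units of total variance, a school mean has variance 0.05 between schools plus 0.95/75.8 = 0.0125 within, 0.0625 in all. The between-school share is 0.05/0.0625 = 80%.

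Adjust with a pupil-level slope of 0.695, taking equal between-school variance at both times and school-level correlation ρ. The variance becomes 0.05 × (1 + 0.483 − 2 × 0.695 × ρ) + 0.0125 × 0.517.
- ρ = 0.3: 0.05 × 1.066 + 0.0065 = 0.0598. √(0.0598/0.0625) = 0.978, so the SE falls by about 2%.
- ρ = 0.695: 0.05 × 0.517 + 0.0065 = 0.0323. The root of the ratio is 0.719, so the SE falls by about 28%.
- ρ = 0.9: 0.05 × 0.232 + 0.0065 = 0.0181. The root of the ratio is 0.538, so the SE falls by about 46%.

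**The case against.** Several points on the other side stand.

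- **Baseline is not excluded.** The regression sentence could include it. The Discussion mentions an analysis plan prepared by a statistical expert, which is not shown, and covariate lists usually sit there. However, the article does fix an unadjusted test and a raw difference of means. That is a stated choice, and what can be criticised is that adjustment remains optional.
- **Ranking and time point are not stated.** A reader might infer that section 3.9 declares an unadjusted test of follow-up scores to be the confirmatory analysis. It does not: it ranks no analyses, names no time point and does not say whether raw or change scores are compared. It is only the one comparison to which the article commits.
- **No bias.** A reader might infer that a chance gap makes part of the effect spurious. Under randomisation the unadjusted difference is unbiased, and chance imbalance is random error that a valid standard error covers. Obtaining a valid standard error here means accounting for schools, a separate matter that baseline adjustment does not settle.
- **No halving of the sample.** With r = 0.695, 62.8 × 0.517 = 32.5, or 33 instead of 63 per group, and a reader might take this as the saving. It holds for independent pupils only. With most of the variance of a school mean lying between schools at ICC 0.05, the documents do not support that figure, or a flat 28%, for this trial.
- **Restriction is not ruled out.** Section 3.7 describes no stratification or matching, but it does not exclude them either.

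**Conclusion.** The point holds as one of efficiency and pre-specification. The article commits to an unadjusted comparison and leaves use of the baseline CYRM-32 score open, although the score is collected and the scale has a documented two-month correlation of 0.695. The cost is precision, plus freedom to choose the adjustment after data have been seen; validity is not in question on this ground.

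The size is uncertain. The pupil-level gain of about 28% rests on a two-month correlation and may shrink by the later follow-up. The trial-level gain could be anywhere from negligible to nearly half of the standard error, depending on a school-level correlation that the article does not report. The imbalance figures rest on assumed ICCs and equal arms. Even the low end does not argue against adjustment, since the data are already in hand. The unadjusted plan should be changed, but it is not a fatal flaw.

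**What to change.** 1. Make the primary analysis a regression of follow-up CYRM-32, at one named time point, on arm and the pupil's own baseline CYRM-32, with school accounted for. A school-mean baseline term is optional: it uses one of about six between-school degrees of freedom, and the critical t rises from 2.447 to 2.571.
2. Apply the same model to BRCS, both ERQ subscales and the sadness item, each with its own baseline.
3. Report the adjusted difference with its 95% confidence interval as the effect, and keep the raw difference as descriptive.
4. Record this as a dated amendment that discloses that baseline and first follow-up data were already being analysed.

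No new data are needed. The cost is the amendment, its disclosure as a change made after data became available, and one covariate per model.

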## Discussion

4.

The present study describes the design, implementation and assessment of the effectiveness of an intervention based on the Individual & Environmental Resilience Model (Llistosella et al., 2022) aiming to increase resilience in adolescents at risk. Moreover, the intervention aims to reinforce the resources and protective factors of adolescents, especially self-regulation skills.

Self-regulation skill as an emotional regulation strategy contributes to the resilience process and also has a positive impact on well-being, relationships, and social and psychological outcomes (Azpiazu Izaguirre et al., 2021; Yıldırım and Arslan, 2022).

According to Gross’ model, there are two main strategies for emotional regulation: cognitive reappraisal and emotional suppression (Gross and Thompson, 2007). The first consists in reframing or re-interpreting the meaning of an event in order to experience it more appropriately, reducing negative behavioral and physiological responses (Gross, 2002). The mechanism of the second one is based on the decrease in emotional expression that aims to hide the emotions that individuals are experiencing (Gross and Thompson, 2007). Studies have shown that these strategies often differ in emotional effects and adaptive psychological adjustment. They could be presented either as adaptive strategies or maladaptive strategies, depending on the expected emotional, behavioral, and cognitive outcomes (Aldao and Nolen-Hoeksema, 2012).

The present study is very powerful because: (1) the content validity of the intervention was determined by nine experts and two adolescents at risk from the multidisciplinary expert committee; (2) it will promote different factors related to resilience, such as emotional regulation strategies, social and communication skills, problem-solving and peer support, among others; all of them have been related with resilience and described in the literature (Dray et al., 2017; Gartland et al., 2019; Pinto et al., 2021; Llistosella et al., 2022); (3) it is dealing with adolescence, a period when several biological and psychological factors can affect and modify the normal development of the individual (Azpiazu Izaguirre et al., 2021). It is also a period to lay the foundation for well-being and foster positive development, including resilience (Morrish et al., 2018). Furthermore, resilience-based interventions have been proven effective only among adolescents between 12-to-18 years and not among children under 12 years; (4) It will assess resilience pre and post-intervention, and also at 24 weeks ensuring the assessment of mid and long-term effects of the intervention; (5) a control group will be used to ensure that the effect is due to the proposed intervention; (6) it has been designed as a cluster-randomized school-based intervention to facilitate adolescents participation and engagement; (7) the static analysis plan was developed by a statistical analysis expert from the International University of Catalonia; and finally (8) an expert also reviewed the final version of the protocol. And the intervention has been drafted to be carried out in more than one school, training and tutoring the team to give reliability and stability to the protocol. Recommendations for Interventional Trials (SPIRIT; Guidance for Clinical Trials Protocols, 2021.) were used to develop the *Fostering Resilience Adolescents at Risk* protocol. Additionally, the CONSORT 2010 Checklist was reported in additional file 1.

In the application of this intervention, we consider some limitations. On one hand, the effect of the intervention may be lost in the long term. However, a 24 weeks follow-up is proposed to assess the maintenance of the effect and see if it is necessary to include reinforcement or repeat the intervention after 1 or 2 years to maintain resilient results. On the other hand, there may be some disparities in the effectiveness of the intervention between schools due to the different teams involved. If this is the case, we will propose to improve the trainings so that the teams act as similarly as possible.

Once the intervention will be applied, we will be able to assess its effectiveness. We expect to increase resilience in adolescents at risk and prevent mental health problems through this school-based intervention. Once the effectiveness is demonstrated, nurses from different fields such as primary health care or mental health specialists will have access to the program to be implemented in schools or other sites that work with adolescents at risk. This intervention will give new tools to nursing professionals to increase resilience and coping skills for facing adverse situations during adolescence.

Currently, we have finished the recruiting period and the trial status is “active” at www.clinicaltrials.gov. At the end of the recruitment, we had a total sample of 674 participants from eight randomized schools. The intervention was carried out in 4 schools from January 2022 to spring 2022. We are analyzing the initial data from control and intervention groups at T1 (baseline) and T2.

## Ethical considerations

5.

### Approval

5.1.

The present protocol was reviewed and approved by the Ethics Committee Institutional Review Board of the “Consorci Sanitari de Terrassa” (Ref: 02-21-160-016) on July 26, 2021.

### Consent process

5.2.

The study will be carried out in compliance with current legislation, by following the Biomedical Research Law 14/2007. The confidentiality of participants’ data will be guaranteed, in compliance with Organic Law 3/2018, of 5 December, on the Protection of Personal Data and the guarantee of digital rights and the General Data Protection Regulation (EU) 679/2016.

First, secondary school directors who will participate in this research will sign an agreement and attachment to the study. Second, an online session with parents/carers of the selected schools will be held to explain the study and the intervention. Third, before being registered for the study, the schools will send a letter with all relevant information about the study and the written informed consent form (in both languages, Catalan and Spanish, to parents/carers). Parents/carers will return the informed consent form (ICF) signed and they will keep a copy. ICF from participants will be obtained after an informative session (with age-appropriate information) in the classroom conducted by their teachers and the research team. If the parents/carers give consent, but the adolescents do not want to participate in the study, the decision of the participants will prevail and will be respected. For adolescents with difficulty with written information, visual information sheets will be provided. Each participant will be identified by a serial number and the initials of the first and last name. Only the principal investigator and collaborating researchers will have access to the collected data.

## Ethics statement

The present protocol was reviewed and approved by the Ethics Committee Institutional Review Board of the “Consorci Sanitari de Terrassa” (Ref: 02-21-160-016) on July 26, 2021.

